## Baseline Assessments

The baseline assessment will take place at the first appointment in which the central research team collects informed consent and performs eligibility assessments, unless participants request additional time to consider their participation in the study.

The central research team will collect the following measurements at the practice:

- Fasting fingerprick blood sample, to be analysed for blood lipids (LDL, HDL, total cholesterol, non-HDL cholesterol, total cholesterol/HDL ratio and triglycerides) using a portable lipid testing system, will be taken by the central research team. This blood sample is needed to confirm elevated LDL cholesterol >3 mmol/L,
- Demographic (age, gender, ethnicity and education, number of people in the household), health behaviours (alcohol and smoking), shopping habits and prior knowledge in regards to diet and SFA collected by questionnaire,
- Relevant medical history and all concomitant medication,
- Dietary intake will be collected using a validated web-based 24-h recall dietary questionnaire, which will be completed twice at baseline, at the in-person visit and before the visit at the participant’s home using their own computer. Participants will be given the opportunity to come to the practice to complete their dietary recall if they are unable to access a computer and internet at home,
- Seated systolic and diastolic blood pressure,
- Weight and height.

Participants will also provide their storecard number, which will be used by Tesco to provide their shopping information during the study period.

Each of these measurements and procedures will be detailed in the study manual held at each site.

## Subsequent Visits

The aim of subsequent visits is to assess the efficacy and non-efficacy outcomes of the trial.

Scheduling of follow-up visits is the responsibility of the central research team, who will contact participants to schedule the follow-up assessments. We will make at least three but no more than five attempts, to contact participants by telephone. We will then use other means (letter; email). Additionally, the central research team will ask the participant to complete one 24h dietary recall prior to the follow up appointment.

## Three-month follow up assessment

A follow up and final visit will be completed at least 3 months and no more than 4 months after randomisation to assess the main study outcomes. Therefore, all the measures collected as part of the baseline visit will be repeated following the same procedures and conditions as described above.

The central research team will collect the following measurements at the practice:

- Fasting fingerprick blood sample, to be analysed for blood lipids (LDL, HDL, total cholesterol, non-HDL cholesterol, total cholesterol/HDL ratio and triglycerides) using a portable lipid testing system, will be taken by the central research team,
- Any changes in knowledge with regards to diet and SFA as well as intervention acceptability collected by questionnaire,
- Changes to relevant medical history and all concomitant medication,
- Dietary intake will be collected using a validated web-based 24-h recall dietary questionnaire, which will be completed twice at follow up, once prior to the follow up visit, and a second one at the in-person visit. Participants will be given the opportunity to come to the practice to complete their dietary recall if they are unable to access a computer and internet at home,
- Seated systolic and diastolic blood pressure,
- Weight.

- Changes to drug treatments during the course of the study: the clinical team in the practice will decide which, if any medications need to be adjusted as a result of changes in health status during the course of the study. However, we will ask participants and clinicians to refrain from altering any lipid-lowering medication during the 3-months of follow-up unless strictly necessary.

## Food shopping data

The proposed intervention involves providing participants with a personalised report on their previous shopping at Tesco supermarkets, therefore a partnership has been established with Tesco to obtain participants’ consent to access the loyalty card data. However, if Tesco is unable to fully meet the expectations of this partnership and cannot provide information in “real time” (e.g. before randomization), a contingency plan has been developed to fill this gap. We will ask participants to collect and store their till receipts from Tesco during a baseline period of 4 weeks before randomization and over the intervention period. We will ask participants to provide us with copies of their receipts at the baseline visit and post them to the study team during the intervention period if access to the loyalty card data is not possible. This will allow us to manually code their shopping and generate their feedback report to show “proof of concept” that generating feedback based on previous purchases would be helpful to improve dietary choices.

## Sample Handling

Fingerprick blood samples will be handled, analysed and then disposed as per protocol using a portable lipid testing system. Blood will be taken at baseline and 3 months to estimate changes in biomarkers of cardiovascular disease risk (total, LDL and HDL cholesterol, non-HDL cholesterol, total cholesterol/HDL ratio, triglycerides).

## Alternative scheduling for follow-ups

The central research team will conduct follow up visits at the participant’s home if they agree and the participant is unwilling to attend the practice. If it’s not possible to do in-person visits, we will record self-reported measures of primary and secondary outcomes by telephone, text or email, if possible.

## Participant reimbursement

As a result of participation in the PC-SHOP trial participants will be asked to attend 2 (control) or 3 (intervention groups) study visits at their local GP practice. In order to minimise the burden on participants of claiming travel expenses (providing receipts, recording mileage, completing forms) the research team will offer each participant a £10 gift card at the 3-month study visit.

## Discontinuation/Withdrawal of Participants from Study

Each participant and their GP have the right and can ask to withdraw from the study at any time. In addition, the Chief Investigator may discontinue a participant from the study at any time if they consider it necessary for any reason, including for example, ineligibility (either arising during the study or retrospectively having been overlooked at screening).

If a participant (or their GP) requests to withdraw from the study, we will explain that we would like to use their data up to the point that they have withdrawn, unless they request that we do not do so. The reason for withdrawal will be recorded in the CRF.

Withdrawn participants will not be replaced.

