**Outcome measures**

i. Primary outcome: change in mean SFA intake (% from total energy intake) between baseline and 3 months, measured using 2 x 24h dietary recalls twice (once at baseline and once at 3 months) using a validated web based questionnaire. We will measure intake at an individual level. We selected SFA intake as the primary outcome because this is the main target in most dietary interventions that aim to promote a healthier diet to prevent cardiovascular disease. Evidence from recent randomised trials in populations with high CVD risk showed absolute changes in %SFA intakes of around 4-5% when participants were provided with the appropriate food swaps^6 7^.

ii. Secondary and non-efficacy outcomes:

We will also examine changes in food purchasing patterns, including changes in mean %SFA from total purchases; energy density, total fat, sugar, fibre and salt from purchases; proportion of food items with low SFA (e.g. products with ≤1.5 grams of SFA per 100 grams of the product); mean total cost of the shopping basket (£) between baseline and 3 months. This is objective information collected through the storecard data, but available only at a household level. However, measures of the nutrients from the storecard data are expected to be highly correlated with nutrient intakes as captured by the dietary recalls but not perfectly if some participants buy food for themselves and different food for the rest of their household (i.e. only one in the household could be on a diet).

We will explore changes in other dietary intake measures using the same dietary instruments as for the main outcome, including changes in mean total energy intake, total fat, total sugar, fibre and salt, as well as changes in the intake of high SFA food groups between baseline and 3 months. Since the intervention will propose specific healthier swaps to decrease total SFA intake, changes in some of these other nutrients and food groups can also be expected, particularly to energy intake and total fat, or there may be compensatory increases in other nutrients such as sugar.

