## Randomisation, blinding and code-breaking

Once the blood test taken during the first baseline visit confirms that the participant has raised LDL cholesterol (>3 mmol/L) and after confirming that they have completed a second 24h dietary recall (details in the next section), and provided their Tesco’s storecard details, the central research team will randomise all eligible participants (until we reach our target sample size) with an allocation ratio of 1:3:3 to control or one of the two active interventions using the online RedCap program which ensures full allocation concealment as information on future allocations are not accessible to the person randomising. Allocation will use block randomisation with randomly varying block sizes of size 7. Once randomised, participants will be booked for a second baseline visit in which they will receive their intervention depending on the group they have been allocated to.

Due to the nature of this trial, it will not be possible to blind participants, clinicians or some of the central research team to the treatment allocation. Nevertheless, the primary outcome will be a measure of saturated fat intake collected through a web-based questionnaire which individuals will fill in individually without any involvement from the study team. The brief advice intervention will be delivered by the practice nurse, who won’t be aware of the treatment allocation within the active intervention arms.

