# STATISTICS AND ANALYSIS

## Description of Statistical Methods

The primary statistical analysis of efficacy outcomes will be carried out on the basis of intention-to-treat (ITT). We will endeavour to obtain full follow-up data on every participant to allow full ITT analysis, but we will inevitably experience the problem of missing data due to withdrawal, loss to follow up, or non-response to questionnaire items.

We will analyse the primary and secondary outcomes with a linear regression model with adjustment for practice and baseline values. We will assess the sensitivity of the analysis to different assumptions about missing data using two imputation methods commonly used: completer only analysis and baseline observation carried forward.

The results from the trial will be prepared as comparative summary statistics (difference in means) with 95% confidence intervals. All the tests will be done at a 5% two-sided significance level. The study results will be reported in accordance with the CONSORT (Consolidated Standards of Reporting Trials) 2010 statements. A full detailed analysis plan (including plans for any interim analysis, subgroup analysis, and sensitivity analysis) will be prepared and finalised before any data analysis.

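### Section 8.10 answers a request to withdraw only with full exit and never asks whether the person would still give the 3-month outcomes

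*Protocol*

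**What the plan says.** Protocol section 8.10 sets out what follows a request to leave: "Each participant and their GP have the right and can ask to withdraw from the study at any time". The team's reply to such a request is then: "we would like to use their data up to the point that they have withdrawn, unless they request that we do not do so". Why the person left is noted on the CRF, and "Withdrawn participants will not be replaced". No other response to a request is described.

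Section 11.1 states the aim for the analysis: "We will endeavour to obtain full follow-up data on every participant to allow full ITT analysis". The same sentence goes on to accept that some data will be missing and names withdrawal among the causes. The two methods named for examining missing data are "completer only analysis and baseline observation carried forward".

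Three provisions bear on whether outcomes could be had without a visit:
- Section 8.3 describes the primary outcome as "collected through a web-based questionnaire which individuals will fill in individually without any involvement from the study team".
- Section 8.8 offers home visits to people unwilling to come to the practice, and then says "If it’s not possible to do in-person visits, we will record self-reported measures of primary and secondary outcomes by telephone, text or email, if possible".
- Section 5 describes the purchase data: "This is objective information collected through the storecard data, but available only at a household level". Under section 8.4 the supermarket supplies them from the card number.

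**The concern.** The efficacy outcomes have one follow-up time, 3 to 4 months after randomisation (section 8.5.1). Someone who asks to leave before then and is handled as section 8.10 describes contributes no 3-month recall, so no primary outcome. Some of these people may object only to the advice, the reports or the visits, and might agree to two web questionnaires or to continued card data if asked. The protocol never has them asked, and no later analysis can recover data that were not collected.

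The trial is unblinded and the arms differ in what there is to stop. Controls have no session and no reports. The brief-advice arm has one session, and the combined arm adds monthly reports. Requests prompted by the intervention can therefore come only from the active arms. If those who leave changed their diet less than those who stay, an analysis of observed data would flatter the arm they left.

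**Working it through.** **1. What the protocol provides in each situation before month 3**

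| Situation | Provision | 3-month primary outcome |
| --- | --- | --- |
| Misses the session or ignores reports, makes no request | Nothing removes the person; 8.5, 8.5.1 and 11.1 still apply | Still sought |
| Will not come to the practice | 8.8: home visit, then remote self-report | Still sought |
| Hard to reach | 8.5: three to five telephone attempts, then letter or email | Still sought |
| Participant or GP asks to withdraw | 8.10: data used up to that point | No step seeks it |

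Only the last row has a gap. That collection stops there is the plain reading of "we would like to use their data up to the point that they have withdrawn, unless they request that we do not do so"; no sentence says so outright. Purchase data accrue through the study, so those up to the request can be kept.

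**2. Could the outcome be collected?** Storecard data need no visit. Of the two follow-up recalls, one is done before the visit and one at it (8.5.1). The tool is web-based and 8.8 allows remote collection, so the second recall does not depend on attendance either.

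**3. The plan's own sample size.** Inputs from 11.2: difference 3 points, SD 3, 90% power, two-sided 0.05, 10% attrition, control to active ratio 1:3. Normal approximation:
- control n = (1 + 1/3) × (1.960 + 1.282)² × (3/3)² = 14.0
- with attrition, 14.0/0.9 = 15.6, so 16; and 3 × 16 = 48 per active arm.

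The stated 16/48/48 reproduces at an unadjusted 0.05.

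**4. Power by share without a 3-month outcome** (equal loss in all arms, same approximation)

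| Loss | Active v control (3 points) | Active v active (2 points) |
| --- | --- | --- |
| 0% | 93.4% | 90.4% |
| 10% | 90.8% | 87.3% |
| 20% | 87.3% | 83.2% |

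Loss up to the planned 10% is covered for each comparison with control. It is not covered for the comparison of the active arms. Power is the lesser issue.

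**5. Possible bias.** Within an arm, the completer mean minus the mean for everyone randomised equals d × (mean change of stayers − mean change of leavers), where d is the share lost. The bias in a contrast is this quantity in one arm minus the same quantity in the other. The documents give no number of withdrawal requests and no outcome for leavers, so what follows is assumption. Stayers change by -3.
- Leavers would have changed like stayers: bias 0 at any d.
- 5 of 48 leave with no change: 43/48 × (-3) = -2.69, against -3.00 in completers. The gap is 0.31 points, and 0.31/2.69 = 12%.
- 20% leave with no change: 0.8 × (-3) = -2.40, a gap of 0.60.
- If this happens only in the report arm, 0.31 to 0.60 points is 16% to 30% of the 2-point difference sought between the active arms.

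**6. What baseline carried forward would show.** It gives every leaver zero change. With 5 of 48 lost it returns 43/48 × (-3) = -2.69, correct only if leavers truly did not change. If they would have changed by -1, the true mean is (43 × (-3) + 5 × (-1))/48 = -2.79. If by +1, it is (43 × (-3) + 5 × 1)/48 = -2.58. It signals a problem without supplying the missing values, and it cannot be used for anyone who also refuses use of the baseline data.

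**The case against.** A reader might infer that anyone who stops the intervention loses the primary outcome. The document does not say so: 8.10 concerns requests to leave the study, and no provision treats a missed session or an unread report as withdrawal. People who refuse only visits are already served by 8.8.

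A reader might also see a contradiction with 11.1. There is none. That section states an endeavour and, in the same sentence, expects withdrawal to cause missing data.

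A third tempting reading is that the loss favours the interventions by 12% to 30%. The direction is not established. The brief-advice arm has a single session of about 10 minutes, preferably within a week of baseline, after which little is left to stop. Controls joined wanting dietary support (7.2) and receive only blood results, so they too may leave, and one control is 1/16, or 6%, of that arm. The 10% in 11.2 is attrition from all causes, not withdrawal requests by people who did not change, and the 20% case has no source. In the zero-change scenario the planned carried-forward analysis returns the same -2.69.

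Finally, a graded choice may appear in the information sheet or CRF, which are not at hand, and a request to leave entirely must be honoured in any case.

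All of this narrows the point. It does not supply the missing step: 8.10 is where the protocol sets the response to a request, and it describes one response only.

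**Conclusion.** The point holds in a limited form. For a formal request by participant or GP before month 3, section 8.10 as written gives up the primary outcome without asking whether it could still be provided, though the means to collect it remotely are already in the protocol. The loss may differ between arms because only the active arms have something to stop. Its size and direction cannot be derived from the document. The 0.31-point figure rests on 5 of 48 leaving with no change while the rest change by -3, and the gap is zero if leavers resemble stayers. The effect on power is modest: at 10% loss, 90.8% against control and 87.3% between the active arms.

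A smaller matter of wording: since the GP may also make the request, it is unclear whether the pronoun in "we would like to use their data up to the point that they have withdrawn, unless they request that we do not do so" lets the GP refuse use of data already collected. A reader might infer a GP veto, but the sentence reads at least as naturally as referring to the participant, so it needs only clarifying.

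**What to change.** In section 8.10, before full withdrawal is recorded, have the team ask and record which of these the participant chooses:
- (a) stop the session or reports but stay in 3-month follow-up;
- (b) decline visits but agree to the 3-month web recalls, continued storecard transfer, or both;
- (c) withdraw fully, which is honoured.

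State that people choosing (a) or (b) stay in the intention-to-treat analysis in their randomised arm. State that only the participant, not the GP, may decline use of data already collected.

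The cost is protocol and information-sheet wording and one CRF field, with no new visits. The one downside is a further question to someone who is leaving.

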## Definition of End of Study

The end of study is the date the last participant has their last data capture for the 3 month follow-up visit.

## Qualitative sub-study

This qualitative study aims to conduct a qualitative process evaluation to examine the perceived value of the behavioural change techniques used in the intervention and the perceived impact on food purchasing behaviours through semi-structured, one-to-one, telephone interviews with approximately 28 participants in intervention 2 group.

This qualitative study will play a valuable role as part of the process evaluation of the trial and will help in the interpretation of the findings of the trial. If the trial outcome is promising it may point to areas that could be enhanced ahead of any future definitive trial to test the effectiveness of the intervention to reduce LDL cholesterol.

**Recruitment**

Once the main study has finished follow up, we will start recruitring participants from the intervention 2 arm of the PC-SHOP study and who are willing to be interviewed. Forty-five participants are potentially eligible and we will continue to recruit until sufficient numbers and data saturation are achieved, estimated based on experience to be approximately 28 people.

First, participant details (including their postal and email address, and intervention arm they were assigned to) will be accessed via the PC-SHOP intervention study electronic, password encrypted database. This database holds all identifiable data and is accessible by the research team only.

A member of the research team will mail all participant’s (i.e. those in intervention 1, intervention 2 and controls) their blood results, which were obtained as part of their final PC-SHOP study visit. This mailing will also include an invitation letter to be telephone interviewed by a member of the research team. Invitations letters will only be sent to participants who participated in intervention 2.

Interested participants will be encouraged to call or email the PC-SHOP study team to ask further questions and either accept or decline the invitation. If a participant accepts the invitation, a convenient date and time for the telephone interview will be arranged and the participant information sheet (PIS) will be sent. Participants will be free to withdraw at any time prior to and during the interview. Non-respondents will be emailed up to two times via the PC-SHOP shared mailbox [[contact]](mailto:[contact]) after their initial postal invitation to remind them before ceasing to try to make contact. We will continue to recruit until data saturation has been reached or when all participants who are willing have been interviewed.

Data saturation is the point when no new themes emerge during analysis. In line with qualitative methods for data collection, we use a zig-zag approach involving the simultaneous process of data gathering and coding meaning the planned sample size (*N*~28) may either increase or decrease depending on when data saturation is reached. Terminating participant recruitment at the point of data saturation will prevent data over collection.

